#### Sample Size

A conservative approach was adopted for this feasibility study, which emphasizes descriptive and qualitative feedback. Consequently, based on the recommendations for pilot studies (44), we plan to include 80 participants (40 cases, 40 controls) over a 2-year inclusion period. As there are around 280 inpatient admissions per year in the Department of Child and Adolescent Psychiatry, i.e., *n* = 560 potential participants contacted at baseline during the 2 years, this will represent a 14% inclusion rate. We predict that the prevalence of SUDs will be similar to that previously reported (18). A good level of compliance with EMA and Stop-Cannabis is expected, consistent with previous studies that reported high levels of adherence (up to 80%) to similar tools in adolescents with comorbid psychiatric disorders (31, 45), and in adults with associated severe psychiatric disorders (32, 46). An acceptance rate of 80% is expected in the SUD group and 50% for the control group. A 50% retention rate at 1-year follow-up is anticipated based on previous longitudinal studies among adolescents (47). In case of a lower enrollment rate, we will either continue to enroll participants during an additional year (2019) in order to reach the intended sample size or use incentives (e.g., free participation in leisure and sport activities in groups) to encourage participant enrollment.

### EMA and Stop-Cannabis App Tools

#### Ecological Momentary Assessment

The EMA was designed as an app for mobile phones. This application allows several daily self-assessments (e.g., five times a day for 2 weeks at different times of the study/monthly). Data are collected in response to a signal from the EMA app that occurs at various times of the day. The app has been programed to send signals (i) a fixed number of times per day at predetermined times (e.g., at bedtime) and (ii) at random (with a balance between week, weekends, and holidays, with different time intervals in daytime). Participants are also asked to complete self-assessment immediately following substance use.

The same questions are presented regardless of assessment type. There are seven questions in total:
Information relating to substance use:
○Daily use of each substance in list.○Level of withdrawal symptoms during participants’ most recent period of abstinence from 0 (not at all) to 5 (severe).○Level of craving from 0 (no urge) to 5 (extreme urge).Information relating to psychopathology:
○Level of negative affect rate using a brief version of the Positive and Negative momentary Affect Scale (PANAS) (48) adapted for EMA (32). Participants provide ratings of the extent to which they felt each emotion on a 1–5 point Likert-type scale.○Main psychiatric symptoms.Information relating to environment:
○Stressful events.○Activities: physical activity, planned activity, lone activity, social activity with peers, family activity, and online activity.

Participants will be trained on EMA use during the week prior to hospital discharge. They will be asked to respond to any signals within 1 h if possible. Consistent with other EMA protocols, participants will complete 2 days of practice data (not used for analyses), after which they will receive feedback on adequate use and compliance. Participants will then be invited to complete EMA assessments for 2 weeks, as this timeframe appears sufficient to monitor substance use (45). To limit attrition, participants will be paid 30€ for completing the baseline assessment and 10€ for each week of complete EMA data, up to a maximum possible payment of 60€ over 1 year.

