### Data Analysis

#### Variables and Instruments

Table 1 lists the questionnaires and other assessments that will be used at baseline and at follow-up. The reading level of the questionnaires is grade 6. The questionnaires we plan to use to measure addiction are described below. A combination of self- and clinician-report measures with different time scales (i.e., DEP-ADO, 12 months; CAST, 6 months; RECAP, 1 month) will be used to examine whether EMA data are consistent with information collected in the traditional way. The second type of measures relate to psychopathology with the aim of examining the interplay between substance use and psychiatric disorders.

**Table 1 T1:** **Variables examined in the study**.

Variables	Administration	Initial assessment	Month 6	1 year

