#### Statistical Methods

##### Primary Outcomes

Pearson correlations will be used to determine the strength of associations between daily substance use assessed by either EMA, or self-report questionnaire (e.g., CAST), or by clinician-report questionnaire (e.g., RECAP) during the clinical assessment at 6 months. Clinical reliability of the EMA will be endorsed if the correlations are statistically significantly higher than 0.70. Further analyses would be performed to estimate different aspects of reliability of the data collected in line with Perrez et al. (64). The severity of SUDs at baseline should predict the severity of substance use and the level of functional impairment at 1 year at least to comparable levels while using EMA data at baseline compared with traditional methods. Two simple linear regression models will be performed. For both the models, the dependent variable will be the severity of SUDs at follow-up; in one model, the independent variable will be the severity of SUDs based on EMA data (Model A), whereas in the other model, the variable will be severity of SUDs based on self- and clinician-report (Model B). The estimate of the independent variable is expected not to be lower in the Model A than in the Model B.

The dropout rate is expected to be less than 40% at 6 months and less than 50% at 12 months for both the EMA and traditional method, with no significant difference between methods. The results of the satisfaction survey will be estimated by analyzing the percentage of answers and the differences among the different categories using Chi-square analysis.

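### The EMA schedule is internally inconsistent and is not tied to the 6-month comparators in the primary validity test

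*Protocol article*

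**What the plan says.** All references are to the Protocol article.

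- **Start of EMA** (*Ecological Momentary Assessment*): "Participants will be trained on EMA use during the week prior to hospital discharge". Two practice days follow, which are not analysed.
- **Length of EMA** (same section): "Participants will then be invited to complete EMA assessments for 2 weeks, as this timeframe appears sufficient to monitor substance use".
- **A different schedule** (same section, describing what the app allows): "e.g., five times a day for 2 weeks at different times of the study/monthly".
- **Payment** (same section): 30€ for the baseline assessment, plus "10€ for each week of complete EMA data, up to a maximum possible payment of 60€ over 1 year".
- **Validity test** (*Statistical Methods, Primary Outcomes*): daily substance use from EMA is correlated with self-report such as CAST, or with use recorded "by clinician-report questionnaire (e.g., RECAP) during the clinical assessment at 6 months". EMA is endorsed only if the correlations are significantly above 0.70.
- **Look-back periods** (*Variables and Instruments*): "i.e., DEP-ADO, 12 months; CAST, 6 months; RECAP, 1 month".
- **Dropout** (*Statistical Methods, Primary Outcomes*): expected below 40% at 6 months and below 50% at 12 months, for EMA as well as for the traditional methods.
- **Other timing statements**: the abstract places the assessment of EMA validity at 6 months and 1 year. *Outcomes, Primary Outcomes* compares EMA with the initial and the follow-up assessments.

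**The concern.** Three accounts of the EMA schedule stand side by side: one fortnight, repeated or monthly bursts, and a payment cap that matches a third number of weeks. None is linked to the 6-month visit, where the validity correlation is computed. Nor does the text say which EMA period enters that correlation.

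This matters because the correlation feeds a pass/fail rule on a primary outcome. If EMA and its comparator describe different periods, a low correlation can mean either that EMA is inaccurate or that use changed between the two. A change shared equally by everyone leaves a Pearson correlation as it is; change that differs between participants lowers it. Such change is plausible here, because only the cannabis users receive an app intended to reduce use. The plan recognises this for the mixed models, which are run separately for participants with cannabis use disorder so that Stop-Cannabis does not interfere. It states no such separation for the validity correlation.

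EMA dropout at 6 and 12 months also has no meaning unless EMA is scheduled at those times.

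**Working it through.** The article gives no computed figure on this point, so there is none to reproduce. The checks are calendar arithmetic, payment arithmetic and a Fisher z calculation.

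**1. Payment cap**
- If the 30€ baseline payment is inside the 60€ cap: (60 − 30)/10 = 3 EMA weeks, or 1.5 two-week bursts. One burst would pay 30 + 2 × 10 = 50€, and twelve monthly bursts 30 + 24 × 10 = 270€. No whole number of two-week bursts gives 60€.
- If the 30€ is outside the cap: 60/10 = 6 EMA weeks, or three bursts, for a total of 90€.

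**2. Overlap of periods if the two-week instruction is followed literally**

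Take discharge as day 0 (assumption), the 6-month visit as about day 182, and a month as 30 days.
- EMA: 2 practice days + 14 days, ending about day 16.
- RECAP window: 182 − 30 = day 152 to day 182. Overlap is 0 days; the gap is 152 − 16 = 136 days, about 4.5 months.
- CAST window: about day 0 to day 182. It contains the fortnight, which is 14/182 = 8% of it.
- The initial questionnaires are taken in the week before discharge and look backwards, so they do not cover the fortnight either.

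**3. Overlap if a burst is placed immediately before the 6-month visit**
- RECAP: 14/30 = 47% of the window.
- CAST: 14/182 = 8%, unchanged.

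**4. What the 0.70 rule requires**
- n = 40 SUD participants × 0.60 retained at 6 months = 24 (the dropout bound in the plan).
- Test of ρ = 0.70 with SE = 1/√(n − 3) on the Fisher z scale, one-sided 5%. The plan states 0.05 only for a secondary comparison, so carrying it over is an assumption.
- Smallest passing r at n = 24: tanh(atanh 0.70 + 1.645/√21) = tanh(0.867 + 0.359) = 0.84 (0.86 if two-sided). At n = 40 it is 0.81.

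**5. How change in use affects the chance of passing**

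Model: expected r = same-period agreement × stability of use between the two periods. Same-period agreement is set at 0.90. Neither 0.90 nor the stability values are in the document.

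| Stability | Expected r | Chance of passing, n = 24 | n = 40 |
|---|---|---|---|
| 1.0 (no change, or aligned periods) | 0.90 | 87% | 98% |
| 0.9 | 0.81 | 33% | 47% |
| 0.8 | 0.72 | 7% | 8% |
| 0.7 | 0.63 | 1% | 1% |

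Even an error-free EMA (agreement 1.0) has an expected r of 0.70 at stability 0.7, and would pass about 5% of the time.

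**The case against.** The strongest reply is that repeated EMA was plainly intended. The app description allows bursts at different times, payment runs over 1 year, the outcome definition compares EMA with follow-up assessments, the regression models refer to EMA data at baseline as though there were later data, and EMA dropout is given at 6 and 12 months. On that view the two-week sentence describes the first burst, or the length of each burst. The flow-chart and the figure on EMA during follow-up are not available here and may carry dates, and a journal article need not print a full calendar. If the cap excludes the baseline payment, it funds exactly three two-week bursts.

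Much of this stands. A reader might infer that EMA is collected only once and that the validity test is therefore bound to fail. The documents support neither step. A single burst is one reading, and failure depends on a stability of use that is nowhere stated. Nor do both comparators miss the fortnight, since CAST's look-back contains it. *Variables and Instruments* also says that different time scales are used on purpose, and the study is a pilot with a descriptive emphasis.

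What the reply does not remove is the conflict in the printed text. The only instruction addressed to participants is one fortnight; the alternative is an example of what the app can do. No visible section places EMA near the 6-month visit or names the EMA period to be correlated. Different time scales can be intended and still need to cover a common period when agreement is judged by a fixed threshold.

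**Conclusion.** The point holds as an inconsistency that reaches a primary criterion. The statements on EMA timing and payment do not describe one schedule, and the 6-month validity correlation and the 6- and 12-month dropout limits need EMA data that the two-week instruction would not produce.

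If that instruction is followed as written, overlap is nil with the RECAP window and about 8% with the CAST window, and real change in use could count against EMA. The window figures rest on EMA starting at about discharge. The size of the effect is conditional: under an assumed same-period agreement of 0.90 and n = 24, the chance of passing falls from 87% to 33% at stability 0.9 and to 7% at 0.8. If bursts are in fact placed before the follow-up visits, most of this concern about RECAP goes away and what remains is to say so. The matter is best settled before data collection, because an EMA burst missed before a visit cannot be recovered afterwards.

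**What to change.** Reconcile the passages as follows.

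1. Schedule a two-week EMA burst after discharge and one immediately before each of the 6- and 12-month visits.
2. State that the pre-visit burst is the EMA period correlated with the instruments at that visit. RECAP is the closest match in time (about 47% of its window); CAST is a longer-window comparison (about 8%) and should be interpreted as such.
3. Define EMA dropout at each time point as no data in the burst belonging to it.
4. Make the payment cap match the scheduled weeks and say whether the baseline payment is inside it.

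Alignment with RECAP remains partial, so some real change within the month can still lower the correlation, but the gap of about 4.5 months disappears.

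Cost: some added participant burden and a small amendment. Three bursts pay 30 + 6 × 10 = 90€, which is at most 30€ more per SUD participant, or at most 40 × 30 = 1,200€ in total and less with attrition. If the 60€ cap already excludes the baseline payment, there is no extra payment.

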#### The Stop-Cannabis App

Launched in 2013, Stop-Cannabis is available free on iOS and Android. It has been continuously updated and improved over the past 3 years, in response to users’ suggestions. When people use the app for the first time, they are asked to document their objectives and choose a quitting date. The app has several modules. First, it allows users to assess their cannabis usage profile (including motivations for use and severity of cannabis use) *via* different assessments (49). Users then receive an individually tailored feedback message that includes links to online psychoeducation and complementary resources. Second, motivational messages are regularly delivered using push-notification technology at different stages of the quitting process, on the basis of updated information regarding current substance use, the selected quitting date, and exposure to situations associated with a high risk of relapse documented by high levels of craving or irritability. Third, the app includes messages on how to cope with craving symptoms or emotional difficulties to enhance participants’ insight into contextual factors for substance use. Fourth, positive reinforcers, such as the number of days since quitting the substance and the amount of money saved, are displayed on the main screen and can be personalized (Figure 1). Fifth, a discussion forum called “The Tribe,” moderated by a psychologist, is available for all users to encourage discussion, mutual support, and information sharing. Sixth, the app includes direct access to a website^2^ for additional information about substance use and online motivational interviewing training.

**Figure 1 F1:**
[figure not shown]
**Ecological momentary intervention “Stop-Cannabis.”**
*Notes*: screenshots of the welcome page, the Feedback page, and the main screen with the benefits of change. Adapted from: Monney et al. (39).

The app will automatically monitor the number of times each participant opens the app and records the number of times participants looked at or used each element. A Unique Device Identifier (UDI) is used to connect the participants’ device to the study database and will be replaced in the data set with a random ID for anonymity. After study completion, the UDIs will be automatically deleted from users’ devices. The app will be available for participants in the intervention group for 12 months. After this period, the app will automatically stop data collection. However, participants are free to use the app for as long as they want.

### Design

#### Screening

The study flowchart is shown in Figure 2. Each patient admitted to the Department of Child and Adolescent Psychiatry at the Pitié-Salpêtrière University Hospital during the study recruitment phase will be systematically screened for SUDs and eligibility at admission. The DEP-ADO questionnaire (50) will be used in the study to document substance use in the previous 12 months. The complete questionnaire is available free online^3^. The screening question will be “During the last twelve months, how often have you [has X] used one of the following substances: alcohol, cannabis, cocaine, inhalant/solvent, stimulant, hallucinogen, or heroin” (examples and trivial names are provided for each substance). For each substance, participants and their families will have the options of answering: “Never,” “Occasionally,” “Once per month,” “Once or twice per week,” “More than three times per week,” or “Daily.” The clinician version of the DEP-ADO will be completed by the clinician involved in usual care after an interview with the adolescent and his/her family. The self-report version will be completed by the adolescent, with assistance from a specially trained member of the paramedical staff. Assessments will be carried out within 3 days following admission and repeated after 1 week as an inpatient, and again if necessary (especially if the clinical condition is not compatible with self-assessment).

**Figure 2 F2:**
[figure not shown]
**Flow-chart of the study**. *Notes*: SUD, substance use disorders; DEP-ADO, the questionnaire used for participants’ screening, is detailed in Section “Screening”; EMA, ecological momentary assessment; TAU, treatment as usual.

Urinary drug tests will be performed on all adolescents hospitalized in the Department of Child and Adolescent Psychiatry during the study recruitment phase. The tests screen for the presence of cannabis, cocaine, opiates, and amphetamines. In the interest of having as broad as possible a representation of the target population, we will include as “screen positive” those who answer at least “occasionally” to use of cocaine, inhalant/solvent, stimulant, hallucinogen, or heroin, and/or at least monthly use of cannabis or alcohol, and/or when their urine test indicates the presence of one of these substances.

#### Assessment to Determine Eligibility

All youths screened positively for substance use will be reported to the hospital’s liaison addiction unit (ECIMUD, a French acronym for *coordination and medical care team for addictive disorders)* for proper diagnosis and care. Systematic evaluation of the substance use and habits will be conducted *via* a semi-structured interview, which allows for scoring the RECAP index, the clinician version of the DEP-ADO, and the Cannabis Use Screening Test (CAST), a self-reported scale that focus on use of cannabis in the previous 6 months (51). Final diagnoses of SUDs will be made by one of the ECIMUD senior psychiatrists using DSM-5 criteria (52).

#### Initial Clinical Assessment and Follow-Up

Participants (i.e., adolescents with SUDs and control subjects) will be approached by a researcher involved in the project (either a clinician specialized in child psychiatry or a master’s level psychologist) who will explain the study and obtain written informed consent from parents or guardian and assent from the adolescent. Participants will be assessed in the week prior to hospital discharge for sociodemographic data, psychosocial information, psychopathology, and substance use (see Variables and Instruments). All youths will be assessed in face-to-face interviews by a specially trained master’s level psychologist at 6-month and 1-year follow-up.

### Data Analysis

#### Variables and Instruments

Table 1 lists the questionnaires and other assessments that will be used at baseline and at follow-up. The reading level of the questionnaires is grade 6. The questionnaires we plan to use to measure addiction are described below. A combination of self- and clinician-report measures with different time scales (i.e., DEP-ADO, 12 months; CAST, 6 months; RECAP, 1 month) will be used to examine whether EMA data are consistent with information collected in the traditional way. The second type of measures relate to psychopathology with the aim of examining the interplay between substance use and psychiatric disorders.

**Table 1 T1:** **Variables examined in the study**.

Variables	Administration	Initial assessment	Month 6	1 year
**Substance use**				
DEP-ADO	Clinician-report self-report	X		X
RECAP Index	Clinician-report	X	X	X
CAST	Self-report	X	X	X
ICSU	Self-report	X		X
Misuse of caffeinated sodas	Self-report	X		X
Urinary screening test	Biological test	X		
**Psychopathology**				
K-SADS-PL	Semi-structured interview	X		X
Ado DIB	Self-report	X		X
ARI	Parent-report	X	X	X
	Self-report			
UPPS-P	Self-report	X	X	X
C-GAF	Self-report	X	X	X
**Other variables**				
Age, gender, academic status, socioeconomic status	Parent-report	X		
ACE	Self-report	X		
Satisfaction questionnaire	Self-report		X	X
CSSRI-EU	Clinician-report	X	X	X

*DEP-ADO, RECAP Index, CAST, Cannabis Use Screening Test; ICSU, Compulsive Internet Use Scale; K-SADS-PL, Kiddie-SADS-Present and Lifetime Version; Ado DIB, Adolescent Diagnostic Interview for Borderline Patients; ARI, Affective Reactivity Index; UPPS-P, Impulsive Behavior Scale; C-GAF, Children’s Global Assessment of Functioning; ACE, Adverse Childhood Experiences Questionnaire; CSSRI-EU, Client Sociodemographic and Service Receipt Inventory-European Union*.

##### Substance Use

The RECAP index is a clinician-reported questionnaire systematically used for standardized collection of information regarding substance use during the last month in outpatient addiction centers in France, recommended by the EMCDDA (European Monitoring Centre for Drugs and Drug Addiction) (available at http://www.ofdt.fr/enquetes-et-dispositifs/recap/presentation/).The CAST is a 6-item self-reported scale that focuses on the use of cannabis in the last 6 months, validated in French (51).The Compulsive Internet Use Scale (ICSU) is a 14-item self-reported scale that focuses on compulsive internet use (53), validated in French (54).The pattern of use of caffeinated sodas will be assessed using a clinician-reported scale previously used in a French outpatient non-clinical sample (55); items are based on Goodman’s criteria for addiction (56).

##### Psychopathology

The Kiddie-SADS-Present and Lifetime Version (K-SADS-PL) is a semi-structured interview used to assess psychiatric disorders (57).The Affective Reactivity Index (ARI) is a 7-item clinician-reported scale that focuses on distinct domains of irritability (i.e., tonic and phasic), validated in English (58).The Impulsive Behavior Scale (UPPS-P) is a 20-item self-reported scale that focuses on distinct domains of impulsivity (i.e., sensitivity to positive and negative emotions, lack of perseverance, lack of premeditation, and sensation-seeking), validated in French (59).The Adolescent Diagnostic Interview for Borderline Patients (Ado DIB) is a self-reported questionnaire that assesses the diagnostic criteria for borderline personality disorder. Translation and validation in French are provided by Guilé and colleagues (60).Overall functioning will be measured using the Children’s Global Assessment of Functioning (C-GAF), one of the most widely used measures of the overall severity of adolescent disturbance (61).

